### Trial design

This study is a cross-over (within-subjects) RCT conducted at the Smart-Aging Research Center (Institute of Development, Aging and Cancer, Tohoku University), Sendai City, Miyagi Prefecture, Japan. All participants will perform both experimental and control conditions (in other words, all participants will act as their own controls). This study (version 1.0) was registered with the University Hospital Medical Information Network (UMIN) Clinical Trial Registry (UMIN000034255) on 1 October 2018.

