### Randomization of interventions

The two intervention conditions will be administered to all participants in two separate sessions (one week apart). Random assignment to the first intervention using an online program (http://www.graphpad.com/quickcalcs/index.cfm) will take place [43]. Each participant is first assigned to a condition non-randomly (the random number generator is seeded with the time and the day). The assignment of each individual is then swapped twice (to make sure it is really random) with the condition assignment of a randomly chosen participant. Half of the participants (15 individuals) will perform the experimental condition first, while the other half will perform the control condition first. The sequence, and with it the assignment to the first intervention condition, is hidden from the researcher that enrolls the participants until the intervention starts to avoid biases; once the intervention begins, the sequence is no longer blinded from anyone.

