#### Stroop task’s RT and ER

The second phase of the data analysis concerns the data collected before and after every IVR intervention, i.e. the results necessary to confirm our main hypothesis (the efficacy of IVR training on cognition).

As previously mentioned, in the Stroop task we will include two measurements, RT and ER: the (incongruent – neutral) contrast, which is assumed to represent Stroop interference, will be calculated. Both (RT and ER) will be analyzed by means of a repeated-measures ANOVA with TIME (before, after) and CONDITION (1PP, 3PP) as within-subject factors. As supplementary analysis, we will check for eventual differences between the two sessions considering only the Stroop task before the vHIE (predicting not differences). According to our hypothesis, we predict finding a shorter RT and lower ER after the vHIE in 1PP compared to 3PP.

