These results would contribute on different levels: from a theoretical perspective, this study would be another proof that the illusion of ownership over the virtual body is extremely effective and can be manipulated in order to arise effects on different levels (perhaps motor and cognitive). The simple fact that it is possible to show some effects consequent to the virtual illusion, comparable to the real ones, means the virtual movements are as effective as the actual ones. Our idea is that the SoBO (here the main variable manipulated through the perspective) can drive other aspects, such as motor function, and those, in turn, can drive others, such as cognitive functions. Theoretical models of motor control should clearly state the body and the sense of body ownership as a variable that can significantly affect the resulted action [68, 69].

From a clinical perspective, these results will have interesting applications: as previously mentioned, the intervention presented here can be very useful for sedentary people or those suffering from cardiopathy to start physical activity in a totally safe and entertaining way, or combining cardio or power exercise, and the IVR training, maximizing the efficacy of both on somatic and cognitive terms. In more extreme situations, patients with motor disorders can perform the virtual training but with the same beneficial effects as physical training [70].

However, this study has some limitations. All participants have to repeat the Stroop task four times (before and after the two IVR sessions). This could have a learning effect, or an effect due to the repetition itself, as a negative consequence. To avoid this, we will randomize the order in which the intervention conditions will be administered, but it is still possible to have a repetition effect. Another potential limitation concerns the control conditions of the intervention: several previous studies using IVR exploit the 3PP as a control condition. In some cases, it seems to have a sort of effect, although the reported effect is smaller than the one of the experimental condition. Finally, a difference between the previous study with a similar design and the current one concerns the type of intervention: in Kujach et al. [17], the training consists of a cycling exercise, while in our study we decided on a running exercise in order to be as consistent as possible with other previous studies with similar IVR setup [33].

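### The primary Stroop ANOVA has no order term, so any practice gain that differs between the two sessions stays in the error term: the test remains valid but can lose power

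*Protocol article*

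**What the plan says.** - **Design.** Trial design: "This study is a cross-over (within-subjects) RCT". Under Randomization of interventions, the conditions are given in "two separate sessions (one week apart", and "Half of the participants (15 individuals) will perform the experimental condition first, while the other half will perform the control condition first".
- **Primary model.** Under Stroop task's RT and ER, the incongruent-minus-neutral contrast for RT and for ER is analysed by "repeated-measures ANOVA with TIME (before, after) and CONDITION (1PP, 3PP) as within-subject factors". Order, period and session are not factors here, and no other section adds one.
- **Learning.** In the Discussion: "All participants have to repeat the Stroop task four times (before and after the two IVR sessions"). The text goes on: "This could have a learning effect, or an effect due to the repetition itself, as a negative consequence". The remedy offered is randomised order, with a reservation: "we will randomize the order in which the intervention conditions will be administered, but it is still possible to have a repetition effect".
- **Supplementary check.** Under Stroop task's RT and ER: "we will check for eventual differences between the two sessions considering only the Stroop task before the vHIE (predicting not differences"). This is a separate comparison and puts nothing into the primary model.

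**The concern.** Counterbalancing protects the mean of a cross-over contrast, but it does not by itself protect the error term. If participants gain more from practice between the before and after runs of session 1 than of session 2, everyone who starts with 1PP has their 1PP-minus-3PP contrast moved one way. Everyone who starts with 3PP has it moved the other way by the same amount. An analysis that ignores order treats this systematic split as random scatter between participants. The standard error is then too large, the actual type I error falls below the nominal 5%, and power is lost.

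The target was 28 participants, with 30 recruited, so there is little spare power. If drop-out leaves the orders unequal, the two shifts no longer cancel fully and part of the practice difference enters the estimate.

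**Working it through.** **Inputs from the protocol article.** Two orders of 15 (Randomization of interventions); TIME and CONDITION as the only factors (Stroop task's RT and ER); α = 0.05, power 0.8, N = 28, recruitment of 30 (Sample size).

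**Inputs not in the documents.** The size of any practice effect, the numerical effect size, the SD, the within-person correlation and the sidedness of the test. These are assumed below and π is shown as a range.

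**The plan's own figure.** N = 28 cannot be rebuilt from the stated inputs, because the moderate effect has no number. A two-sided paired t-test gives 28 at a standardised difference of 0.55 and 34 at 0.5; a one-sided test at 0.5 gives 27. I use 0.5 SD, two-sided, as a working assumption.

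**Step 1: reduce the test.** The TIME × CONDITION test is a one-sample t-test on D = (after − before in 1PP) − (after − before in 3PP). Scale D so that its SD within an order is 1.

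**Step 2: add practice.** Let p1 and p2 be the before-to-after practice changes in interference in sessions 1 and 2, and π = p1 − p2. Then

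- 1PP first: D = τ + π + e
- 3PP first: D = τ − π + e

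where τ is the true effect. With 15 per order the mean of D is τ, so there is no bias.

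**Step 3: error variance.** Ignoring order, E[s²] = 1 + π² × n/(n − 1). For n = 30 the standard error is too large by a factor of √(1 + π² × 30/29). With an order term the residual variance is 1 on n − 2 = 28 df.

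**Step 4: numbers.** True effect 0.5 SD, 15 per order, two-sided 0.05, by simulation:

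| π | SE factor without the term | Power without | Power with | Type I error without |
|---|---|---|---|---|
| 0 | 1.00 | 0.75 | 0.75 | 5.0% |
| 0.25 | √1.065 = 1.03 | 0.73 | 0.75 | 4.3% |
| 0.5 | √1.259 = 1.12 | 0.67 | 0.75 | 2.9% |
| 0.75 | √1.582 = 1.26 | 0.57 | 0.75 | 1.5% |
| 1.0 | √2.034 = 1.43 | 0.44 | 0.75 | 0.6% |

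With the term, type I error stays at about 5%. With a true effect of 0.53 SD, chosen to give 80% power at π = 0, the pattern is the same. Power without the term is 80%, 78%, 73%, 63% and 50% down the rows, against 80% with it.

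**Step 5: unequal orders.** With 15 and 13 completers the bias is π × (15 − 13)/28 = 0.071π. That is 0.018 SD at π = 0.25 and 0.071 SD at π = 1.0.

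**Step 6: which learning counts.** In arbitrary units over the four runs:

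- Equal gains per run (0, −1, −2, −3): session changes −1 and −1, so π = 0.
- A single step between sessions (0, 0, −1, −1): changes 0 and 0, so π = 0.
- Flattening gains (0, −1, −1.5, −1.75): changes −1 and −0.25, so π = −0.75 units.

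Only the last kind reaches the TIME × CONDITION error term. If 1PP versus 3PP were instead tested on the after runs alone, those are runs 2 and 4, and even equal gains per run would leave a shift of 2 units.

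**Step 7: the supplementary check.** It uses only the before runs. π is a difference between two before-to-after changes, so this check cannot estimate it.

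**The case against.** The strongest reply is that little may be lost. Several parts of it stand.

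- **Learning is a possibility only.** A reader might infer that the protocol expects learning. The Discussion says only that it could occur, and the Stroop section predicts no difference between sessions in the before runs.
- **Most forms of learning cancel.** A reader might infer that all practice is counted as random error. Practice that speeds incongruent and neutral trials equally drops out of the interference score, and equal gains per run drop out of TIME × CONDITION. Participants are also trained on the response rule beforehand, which may blunt early gains. That practice is larger in session 1 is a plausible assumption, which the documents do not state.
- **The large losses need a large π.** At 0.25 SD the cost is two points of power. The losses at 0.75 and 1.0 need a session difference in practice larger than the assumed treatment effect, and nothing in the documents supports that size.
- **Validity is intact.** A reader might infer a biased estimate or false positives. With 15 per order the estimate is unbiased and the test is conservative, and the bias from 15 versus 13 completers is small.
- **Other outcomes.** A reader might extend the loss to heart rate, questionnaires, TDMS and fNIRS. The Discussion raises repetition for the Stroop task only, and no loss was shown elsewhere. In the heart-rate analysis, for example, a session shift common to running and walking cancels from the speed × condition interaction.

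It can also be said that an unseen analysis plan might add order. The article, however, names the factors of its primary model, so the omission concerns something it has fixed.

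**Conclusion.** The point holds as one of efficiency. The design creates two orders to deal with possible learning, and the primary model then makes no use of the order variable. The cost depends wholly on π, which the documents do not give: nothing at π = 0, about 2 points of power at 0.25, about 8 at 0.5 and about 31 at 1.0, the last being an extreme case. These figures assume n = 30 in equal orders, a two-sided 5% test, a true effect of 0.5 SD of the contrast, normal errors and TIME × CONDITION as the test of interest. The algebra is certain; the size of the loss in this trial is not. A significant result from the planned ANOVA with balanced orders would still be valid, so the change is advisable but not essential.

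**What to change.** Add ORDER (1PP-first, 3PP-first) as a between-subject factor, with its interactions, to the Stroop RT and ER ANOVA. Take the TIME × CONDITION test from the order-adjusted error term with the two order means weighted equally. Equal weighting also removes the bias from unequal completers.

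If a mixed model is preferred, its fixed effects should be CONDITION, TIME, CONDITION × TIME, SESSION and SESSION × TIME. CONDITION × TIME must be there because it is the contrast under test. The covariance should have participant, participant-by-session and participant-by-time random effects, or be unstructured within participant; a random intercept alone would not reproduce the ANOVA's error term.

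The cost is one sentence in the analysis section and one residual degree of freedom (29 to 28). If π = 0, power at 0.5 SD goes from 0.754 to 0.753. No new data are needed. The same term may be added to the other 1PP versus 3PP comparisons for consistency.

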#### fNIRS data

The optical data from fNIRS will be analyzed based on the modified Beer-Lambert law [57]. We will set the sampling rate at 10 Hz and analyze the difference between O2Hb and HHb signals.

We will employ the general linear model to identify O2Hb and HHb hemodynamic brain responses with reference to experimental factors. If necessary, we will combine few adjacent channels in order to create region of interest (ROI) [58] according to the LBPA40 anatomical labelling system [59].

Then, the changes in the concentration of O2Hb and HHb for each channel will be treated according to the following steps:
Excluding skin blood flow (i.e. heartbeat pulsations) from raw data by using the specific software provided.Pre-processing each channel using 0.01–0.5 Hz bound pass filter to account for the effects of Mayer waves, high-frequency fluctuations, and baseline drift [60].Performing a 3-s moving average to smooth the raw O2Hb concentrations [61, 62].We will use the color-word matching Stroop task in an event-related design which presents each neutral, congruent, and incongruent conditions in random order, so we will pick up the changes related to each condition in the concentration of O2Hb from each channel (or the combined ROIs). In particular, we will calculate the mean of the changes in the concentration of O2Hb 2 s before onset task, as a “baseline,” and 10 s after the onset of the inter-stimulus interval as “vascular response” in each Stroop task condition [46]. That will be necessary because NIRS signals are delayed with respect to participants response [46, 63].Translating the mean of O2Hb concentrations of each channel to normalized values using linear transformations, so that the mean ± standard deviation of O2Hb level in the 2 s of the baseline period is 0 ± 1 (AU). This method will be useful because of the avoidance of the influence of differential pathlength factors among the individuals and that of cortical regions [60, 64, 65].Lastly, the channels over target ROI areas, eventually, will be averaged in each Stroop task condition respectively.

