#### Stroop task

To measure the actual efficacy of the proposed intervention, we will record cortical hemodynamic changes in the participant’s PFC using the functional near-infrared spectroscopy (fNIRS) device before and after every IVR session (either 1PP and 3PP) during the execution of the color-word matching Stroop task (see Fig. 2 a).

We will adopt the Stroop task as previously used in several studies [17, 22, 46–48]. The Stroop task we plan to use consists of 30 trials, including 10 neutrals, 10 congruent, and 10 incongruent, presented in random order. For all trials, two words are displayed on the monitor one above the other: specifically for neutral trials, the upper row consists of XXXX printed in red, white, blue, pink, or yellow, and the lower row shows the words “RED,” “WHITE,” “BLUE,” “PINK,” or “YELLOW” printed in black. For congruent trials, the upper row contains the words “RED,” “WHITE,” “BLUE,” “PINK,” or “YELLOW” printed in the congruent color (e.g. RED was printed in red) and the lower row contains the same color words printed in black. For incongruent trials, the color word in the upper row is printed in an incongruent color (e.g. RED was printed in yellow) to produce cognitive interference between the color word and the color name (i.e. Stroop interference). All words were written in Japanese (hiragana). The lower row is presented 100 ms later than the upper row, in order to achieve sequential visual attention. Between each trial a fixation cross is shown, as an inter-stimulus interval, for 9–13 s to avoid timing prediction [17, 22, 49]. The stimulus remains on the screen for 2 s, independently from the participant’s answer. We will train participants to decide whether the color of the upper word (or letters) corresponds to the color name of the lower word by pressing button 1 on the keypad to give “yes” responses or button 2 to give “no” responses with their forefingers. Of the presented stimuli, 50% were correct (the correct answer is “yes”). We recorded response time (RT) and error rate (ER) as variable.

The Stroop task will be administered entirely via computer (to avoid biases due to presence of the researcher, especially concerning RT); for the present study, the Stroop task has been implemented using E-prime 2.0.

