#### Secondary outcomes

Secondary outcomes are the data extracted from the fNIRS recording, as a neural counterpart of the behavioral measurements. We will focus specifically on O2Hb changes before and after the vHIE in the two conditions (1PP and 3PP).

In addition, we will examine the relation between Stroop task and the induced cortical activation, by means of a correlation between behavioral data from the Stroop task (RT and ER) and optical data from fNIRS. For each trial of the Stroop task (neutral, congruent, and incongruent), we will average the O2Hb data for 2 s before, 2 s during, and 10 s after the presentation of the stimulus (expecting a peak at 4–11 s after the display); also in this case, we will obtain the Stroop interference by subtracting (incongruent-neutral) O2Hb data. As for the other outcomes, the main comparison to test our hypothesis will be between 1PP and 3PP.

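### O2Hb is scaled by the SD of a 2-s baseline taken after 3-s smoothing: an unstable divisor whose unit is left open, so the secondary fNIRS contrast can lose much of its precision

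*Protocol article*

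**What the plan says.** The *fNIRS data* section fixes the processing in order. The signal is sampled at a stated rate ("We will set the sampling rate at 10 Hz") and, after removal of skin blood flow, band-pass filtered ("Pre-processing each channel using 0.01–0.5 Hz bound pass filter"). It is then smoothed: "Performing a 3-s moving average to smooth the raw O2Hb concentrations". Next, a baseline and a response are extracted for each trial type. For the baseline, "we will calculate the mean of the changes in the concentration of O2Hb 2 s before onset task"; the response covers "10 s after the onset of the inter-stimulus interval". Then comes the scaling, "so that the mean ± standard deviation of O2Hb level in the 2 s of the baseline period is 0 ± 1 (AU". Its stated purpose is to remove the influence of pathlength factors that differ between individuals and between cortical regions. The same section also names a general linear model, without saying whether model estimates or the scaled means are the O2Hb outcome.

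The timing comes from the *Stroop task* section: each stimulus stays on screen for 2 s, followed by a fixation cross "as an inter-stimulus interval, for 9–13 s to avoid timing prediction". There are 10 neutral, 10 congruent and 10 incongruent trials in random order. *Secondary outcomes* makes the O2Hb change the secondary outcome, forms the incongruent-minus-neutral difference, compares 1PP with 3PP, and describes the response as "expecting a peak at 4–11 s after the display".

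**The concern.** The smoothing window (3 s) is longer than the window that supplies the SD (2 s). Neighbouring smoothed values share most of their data, so the SD within the window reflects the local slope of the trace more than its noise. It will often be close to zero. Dividing by it produces occasional very large values.

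If the SD is taken per trial or per condition average, neutral and incongruent responses are divided by different, randomly varying numbers before they are subtracted. The interference contrast then carries the variability of the divisor as well as that of the response.

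In addition, the interval between trials is short relative to the expected response, so part of a baseline can contain the tail of the previous trial's response.

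The secondary outcome is at stake, together with the analyses that relate O2Hb to Stroop performance in the *Correlations* section. The primary outcome, Stroop reaction time, is not affected.

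**Working it through.** The protocol states no precision figure for fNIRS, so there is none to reproduce.

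**1. Size of the divisor.** At 10 Hz the baseline is 2 × 10 = 20 samples and the moving average spans 3 × 10 = 30. For white noise passed through a 30-sample average, the correlation at lag k is 1 − k/30. The expected within-window variance, as a fraction of the true variance, is 1 minus the mean pairwise correlation, that is, (mean lag)/30. For 20 samples the mean lag over all pairs is (20 + 1)/3 = 7, so the fraction is 7/30 = 0.23 and the root-mean-square SD is √0.23 = 0.48 of the true SD. This is before the band-pass filter, which makes the values still more alike.

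Simulation with the stated filter and smoothing, for three assumed noise types:

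| Noise | Median 2-s SD ÷ whole-signal SD, before → after smoothing | CV of the 2-s SD, before → after | 95th/5th percentile of the SD, before → after |
|---|---|---|---|
| White | 0.59 → 0.32 | 0.50 → 0.61 | 5.9 → 8.8 |
| 1/f | 0.37 → 0.19 | 0.55 → 0.66 | 6.7 → 10.0 |
| 1/f² | 0.17 → 0.10 | 0.60 → 0.69 | 8.6 → 12.8 |

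Most of the instability is there before smoothing, so the short window is the main cause and smoothing adds to it.

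**2. Overlap.** Let U be the interval, assumed uniform on 9–13 s. Counted from the previous stimulus onset, the next stimulus starts at U + 2 and its baseline runs from U to U + 2. The plan's response window is 2–12 s after onset.

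- Any overlap with the 4–11 s peak range: P(U < 11) = (11 − 9)/4 = 50%. Mean overlap is (1/4)∫(11 − U)dU over 9–11 = 2/4 = 0.5 s, or 25% of the baseline.
- Any overlap with the 2–12 s response window: P(U < 12) = (12 − 9)/4 = 75%. The baseline lies wholly inside when U ≤ 10, which is 25%. Mean overlap is (1 × 2 + 2)/4 = 1 s, or 50% of the baseline.
- The response window runs into the next stimulus when U + 2 < 12, again 25%.
- Range without the uniform assumption: at U = 9 the baseline lies wholly inside both windows; at U = 13 it overlaps neither.

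**3. Consequence for the contrast.** A cross-over simulation took 1,500 participants through four runs of 30 trials and formed the before/after, 1PP/3PP difference of incongruent minus neutral. Assumptions: a gamma-type response convolved with the 2-s stimulus; neutral and congruent amplitude 1; incongruent amplitude 1.4 on average, raised by 0.4 only after 1PP; noise made of a 1/f part and a 0.1 Hz oscillation; pathlength varying between participants. Retained information is (d for the scaling ÷ d unscaled)². Approximate power is Φ(d√28 − 1.96), using the protocol's calculated 28 participants, a number derived for reaction time.

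| Divisor | Standardised effect d at noise 0.5 / 1 / 2 | Information kept | Approximate power |
|---|---|---|---|
| None | 0.61 / 0.40 / 0.23 | 100% | 0.89 / 0.56 / 0.23 |
| 2-s SD per trial | 0.29 / 0.29 / 0.17 | 23% / 54% / 58% | 0.33 / 0.34 / 0.15 |
| 2-s SD of condition average | 0.15 / 0.11 / 0.13 | 6% / 7% / 31% | 0.12 / 0.08 / 0.10 |
| SD of all 30 baselines of a run together | 0.58 / 0.43 / 0.24 | 91% / 118% / 110% | 0.86 / 0.63 / 0.25 |
| Whole-run SD | 0.51 / 0.40 / 0.23 | 72% / 104% / 104% | 0.77 / 0.57 / 0.23 |

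Noise is expressed relative to the response amplitude. With 1,500 participants each d has a Monte Carlo error of roughly 1/√1500 = 0.03, so small differences between rows should not be read closely.

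**The case against.** The strongest reply is that the protocol never says the SD is taken separately for neutral and incongruent trials. It speaks of normalising each channel, and its purpose, removing pathlength differences between people and regions, is met by one scale per channel. On that reading little is lost, and an article may leave the unit to a fuller document. This stands in part: separate scaling by trial type cannot be stated as fact. But the step just before it extracts baseline and response by trial type, and the averaging by trial type over the ROI channels comes afterwards, which points towards a per-trial or per-condition SD. The 2-s window and its place after smoothing are fixed in this text.

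Further points that stand:

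- The overlap is partial. Because trial order is random, it falls on neutral and incongruent trials alike on average.
- Smoothing is not the main culprit.
- The size of the loss rests on assumed noise and response shape; at the highest noise the per-trial loss is modest (0.23 to 0.17).
- The McNemar test in *Correlations* works on binary outcomes, so extreme values have little leverage there, although wrong signs remain possible.
- A general linear model is already planned. That helps only if its estimates are the outcome, which the text does not say.
- The methods cited for the scaling cannot be examined here.

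**Conclusion.** The point holds as a badly fixed analysis step on a secondary outcome. The instability of the 2-s SD follows from the stated sampling rate, window and step order, and appears under all three noise models. The loss of precision is conditional: in the simulation 42–77% of the information is lost with a per-trial SD and 69–94% with a condition-average SD, but little or none with an SD pooled over a run's baselines. The overlap figures of 50% and 75% rest on the stated timings plus a uniform interval.

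A reader might infer more, and the document does not support it:

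- That the fNIRS outcome is mostly noise. This would need the SD unit to be known and the noise to be as assumed; neither is in the text.
- That every baseline contains the previous response. At the longest intervals none does.
- That the overlap biases the interference contrast. Random order makes it mainly added variance.
- That the scaling would produce a false 1PP effect. No type I error was examined. A shift in baseline variability specific to 1PP is conceivable but not shown.

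**What to change.** Either of two changes to the *fNIRS data* section would do.

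1. Keep the scaling but change the divisor: one SD per participant and channel, taken from a long reference and applied unchanged to all trial types, both times and both conditions. The reference can be all baseline samples pooled around their common mean, the GLM residuals, or the whole filtered run. Such a divisor multiplies a participant's entire contrast in that channel by one positive constant, so it cannot create differences between trial types or sessions, and it still serves the pathlength purpose. The simulation used one SD per run, not one across all four runs, and did not test GLM residuals. The whole-run SD kept 72% of the information at the lowest noise, so it is the less attractive reference if responses are strong.

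2. Make the incongruent-minus-neutral contrast of betas from the GLM already named the O2Hb outcome. The model can represent overlapping responses over the whole run, which also deals with the short interval.

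The section should say which of the two feeds the ANOVA and the correlation analyses. Dropping the 3-s smoothing is optional once the divisor is changed. The cost is wording only, with no new data; the small downside is less direct comparability with earlier studies that used epoch z-scores.
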